## Statistical analysis plan

The data collected in the antimicrobial audit form will be analysed after entry into the excel form. The antimicrobial consumption analysis will be done using Microsoft excel. The descriptive data analysis will be done using Statistical package for the social sciences (SPSS) Version 23. The rate of surgical site infection till 30 days after surgery (90 days if implant) will be expressed as events per person-time, separately for clean, clean-contaminated, contaminated surgeries. All secondary endpoints will be expressed as mean, standard deviation (if the variable is quantitative) or as frequency, percentage (if the variable is categorical). The rates of primary outcome and secondary outcomes measured at the study centres in post-intervention will be compared with the pre-intervention/baseline data to assess the impact of the intervention. Chi-square test, independent sample t test or Mann-Whitney U test will be used for the statistical comparisons.

Plots and pivot tables will be generated using statistical software or excel as appropriate. The analysis will be conducted separately for clean, clean-contaminated and for contaminated surgeries. A sub-group analysis will also be conducted as per the level of fidelity.

Kaplan Meier curves will be plotted to demonstrate the incidence rates of surgical site infections. The difference in the rate of surgical site infections between the nature of surgeries (clean, clean-contaminated, contaminated surgeries), or any other exposure categories will be statistically tested using the log-rank test. A Cox proportional hazard model will be constructed to identify the predictors of surgical site infections.

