Despite these guidance documents in place, SSIs remains a substantial cause of morbidity, mortality and economic burden in hospitalized surgical patients especially in LMICs. Recent studies from India showed a comparatively lower yet substantial incidence of SSI of about ~12.5 % in general surgical patients with most common pathogen associated with SSI being beta-haemolytic *Streptococci* and *Staphylococcus aureus*.^7^ The study found that the prevalence of SSI was higher (17.7%) in emergency surgeries as compared to 12.5% in elective surgeries probably requiring judicious and timely use of surgical prophylaxis as per recommendations, extra pre-operative and intra-operative care to lower overall SSI incidence rates.^7^ Similar rates were found in a recent large pragmatic multicentric randomized controlled study in LMICs with overall SSI rate of 22% (15.5% for clean-contaminated and 30% for contaminated or dirty surgeries).^8^ A prospective study conducted recently in PGIMS Rohtak, India found incidence of SSI to be ~8% for clean and ~10% for clean-contaminated surgeries.^9^

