# Investigational plan

## General Scheme of Study Design and Study Plan:

Quasi-experiment (pre-post design) will be adopted.

The plan is to adopt a four- phased strategy using mixed-method approach, each addressing specific research question (Figure-1).

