The baseline data collection will be done by the trained research associate/ICN nurse for the patients undergoing surgeries as per inclusion/exclusion criteria and the baseline SSI rate in the setting will be calculated from the baseline data collected. The baseline data collection will be done using the standard case record form (CRF) designed for the study which will include collection of data on (but not limited to) parameters like type of surgery, American Society of Anesthesiologists (ASA) physical status score (refer to Annexure-V), timing and antimicrobial agent for surgical prophylaxis, duration of surgery, need for redosing of antimicrobial prophylaxis, and other defined parameters. In addition, the observation of practices of the care delivery team and observation of interactions among care team and patients will be done at this stage. This qualitative assessment will allow the research team to observe points that practitioners may not have reflected on or recollect during interviews. The baseline data collection phase will last for 6 months. No intervention or practice change will be applied in this phase.

**Outcome of Phase-I:** Expected outcome of Phase-I will be to identify the knowledge gaps in the practice, barriers and challenges in adoption of the surgical prophylaxis prevention guidance. The baseline data collection will be done in this phase (pre-intervention data) on the baseline SSIs rates and practice followed in the setting. These findings will be helpful in co-development of the multipronged interventions during Phase-II.

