## Allocation to Treatment Groups and Blinding (if applicable)

Not applicable

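### The impact conclusion rests on unadjusted tests between two periods, so a change in site mix or in case mix within wound class would be credited to the intervention

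*Protocol*

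**What the plan says.** Section 3.1 sets the design: "Quasi-experiment (pre-post design) will be adopted". Section 3.2, on allocation and blinding, reads "Not applicable". Calendar period is therefore the only contrast, and the patients in the two periods are different people.

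Section 3.9 fixes the impact analysis. Outcomes "measured at the study centres in post-intervention will be compared with the pre-intervention/baseline data to assess the impact of the intervention", and "Chi-square test, independent sample t test or Mann-Whitney U test will be used for the statistical comparisons". The synopsis repeats this. The analysis is run separately for clean, clean-contaminated and contaminated surgery, and no other stratification or covariate is named for the pre-post comparison. The only model has another purpose: "A Cox proportional hazard model will be constructed to identify the predictors of surgical site infections". The log-rank test is assigned to comparisons between wound classes or other exposure categories.

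On data, section 3.1.1 lists "parameters like type of surgery, American Society of Anesthesiologists (ASA) physical status score" and duration of surgery among the items on the case record form. Section 3.1.4 says the same parameters are collected after the intervention. On timing, "The baseline data collection phase will last for 6 months".

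Two further sections affect who contributes to the second phase. Section 3.5.1 terminates sites and surgeons that do not comply and stops data collection at such a site. Section 3.1.3 says that staff scoring below 80% in the training assessment are either re-trained or not included.

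**The concern.** With no concurrent control, anything that differs between the periods and affects SSI risk enters the estimated effect. Splitting by wound class deals with one such factor. It does not balance site, urgency, specialty, ASA status, implant use or duration of surgery within a class.

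The protocol's own rules can produce such a difference. Termination for not following the interventions, and exclusion after a failed training assessment, can act only after baseline. The sites and surgeons lost this way could plausibly have had higher SSI rates to begin with. An unadjusted comparison would count their departure as benefit. This bears on the primary conclusion in all three wound classes.

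**Working it through.** **1. The plan's own sample size (section 3.11).** Inputs: 8% to 5%, 12% to 8% and 30% to 20%; two-sided 5%; 90% power; 15% loss. The usual formula for two proportions, with p̄ the mean of the two rates, is

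n = [1.96·√(2p̄(1−p̄)) + 1.2816·√(p₁(1−p₁)+p₂(1−p₂))]² / (p₁−p₂)².

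It gives 1418, 1181 and 392 per phase. Multiplying by 1.15 gives 1631, 1359 and 451, against the stated 1630, 1350 and 450. The figures reproduce. They contain no term for site or covariates, which is consistent with an unadjusted two-proportion test.

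**2. Illustration of a change in site mix, clean surgery.** All inputs below are assumptions except the 8% baseline and the planned size. The documents give no site-specific rates.

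- Seven equal sites average 8%. Two of them have 12%. The other five average (7×0.08 − 2×0.12)/5 = 0.32/5 = 6.4%.
- The two sites contribute to baseline only, their baseline patients stay in the comparison, and the intervention does nothing. The crude rate goes from 8.0% to 6.4%, a difference of 0.016, or 53% of the 3-point target (1.6/3).
- Patients with an outcome per phase: 0.85 × 1630 ≈ 1385.
- Standard error under the null: √(2×0.072×0.928/1385) = 0.00982. Critical difference: 1.96 × 0.00982 = 0.01925.
- Standard error at the assumed rates: √((0.08×0.92 + 0.064×0.936)/1385) = 0.00982.
- P(significant reduction) = Φ((0.016 − 0.01925)/0.00982) = Φ(−0.33) ≈ 0.37, against 0.025 nominally in that direction.

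This assumes that the five remaining sites fill the second phase to its planned size. If they do not, the second phase has 1385 × 5/7 ≈ 989 patients. The two standard errors become 0.01085 and 0.01066, and the probability is Φ((0.016 − 0.02127)/0.01066) ≈ 0.31.

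The result depends on the assumed site rate and on the number of sites lost. At full size:

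| Sites lost | Their clean rate | Second-phase rate | P(significant reduction) |
|---|---|---|---|
| 1 | 10% | 7.7% | 5% |
| 1 | 12% | 7.3% | 10% |
| 2 | 10% | 7.2% | 12% |
| 2 | 12% | 6.4% | 37% |
| 2 | 14% | 5.6% | 71% |

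**3. Would adjustment help here?** In this example the five remaining sites have 6.4% in both phases. A site-adjusted phase effect uses only contrasts within site, so its expected value is zero.

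**4. Room for adjustment.** Expected events at 85% follow-up and the planned rates:

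- Clean: 1385.5 × (0.08 + 0.05) ≈ 180.
- Clean-contaminated: 1147.5 × (0.12 + 0.08) ≈ 230.
- Contaminated: 382.5 × (0.30 + 0.20) ≈ 191.

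A short model could use phase (1), site (6), urgency (1), ASA in two categories (1), specialty in three groups (2), implant (1) and duration (1). That is 13 parameters, or 180/13 ≈ 14 events per parameter in the smallest case. A full list would be phase (1), site (6), urgency (1), ASA 1–5 (4), six specialties (5), open or laparoscopic (1), implant (1), duration (1) and season (3). That is 23 parameters, or about 8 events each, which is too thin.

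**The case against.** **A separate analysis plan may exist, and covariate lists usually go there.** True of the details. But section 3.9 does not leave the matter open: it names the tests by which impact is judged. That is a stated choice.

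**The planned Cox model could carry a phase term.** It could, and using it is the smallest fix. As written it only looks for predictors. The protocol also does not say outright that rates are pooled over sites, but it names no site term or site stratification.

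**The fate of a terminated site's baseline data is not stated.** If those patients were removed from both phases, the site example would not arise. The protocol stops further collection and says nothing about data already held. Surgeon and staff selection within a site would remain.

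Some stronger readings are tempting and are not supported:

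- *Emergency share.* The introduction reports that "The study found that the prevalence of SSI was higher (17.7%) in emergency surgeries as compared to 12.5% in elective surgeries". With an assumed 20-point fall in the emergency share, 0.20 × 5.2 = 1.04 points, which looks like 26% of the 4-point clean-contaminated target. Those rates are not within a wound class, part of the gap may be wound class itself, and the 20-point shift is invented. The figure cannot be carried into one stratum.
- *Season.* The calendar of the second phase would be in Figure 3 and the Gantt chart, which are not shown in the text at hand. Seasonal imbalance is possible but cannot be demonstrated.
- *Secular trend.* An assumed decline of 10% a year over 12 to 18 months would lower an 8% rate by 0.8 to 1.2 points and give a 12% to 22% chance of a significant reduction. Both the decline and the interval are guesses, and adjusting for case mix would not remove this.
- *All covariates are in hand.* Type of surgery, ASA and duration are listed as recorded items. Urgency and implant status appear in the eligibility and follow-up text, so their place on the form needs confirming.

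**Conclusion.** The point holds in a limited form. Section 3.9 judges the intervention's impact by unadjusted tests between two periods, separated only by wound class, and no regression is tied to the phase effect. The protocol's own termination and training rules can change the mix of sites, surgeons and staff after baseline, and following the plan as written would credit that change to the intervention.

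The size cannot be derived from the documents. On assumed site rates of 10% to 14%, losing two of seven equal sites gives a 12% to 71% chance of a significant clean-surgery reduction with no effect. The central example gives 37%, or 31% if the lost patients are not replaced. Losing one site at 10% or 12% gives only 5% to 10%. These figures show that the exposure is real; they are not a prediction.

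A reader might infer that adjustment would make the pre-post contrast causal. It would not. With one 6-month baseline and no concurrent control, a background trend cannot be cleanly separated from the intervention.

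**What to change.** In section 3.9, and in the matching synopsis text:

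1. Within each wound class, make the primary estimate the phase effect from a pre-specified adjusted regression. Either give the planned Cox model a phase term, which stays closest to the person-time wording already there, or use a logistic model reported as a standardised risk difference with 95% CI.
2. Include site and a short list of case-mix variables: elective or emergency, ASA in collapsed categories, specialty group, implant and duration of surgery. Size the list to the roughly 180 to 230 expected events per class. Confirm that urgency and implant status are on the case record form in both phases.
3. Do not adjust for prophylaxis timing, agent or redosing. The template package in Appendix I makes them targets of the intervention, so adjusting would remove part of its effect.
4. Keep the chi-square comparison as descriptive.
5. Add a sensitivity analysis limited to sites that contribute to both phases and, where the calendar allows, one limited to matching months. Show a monthly SSI plot.
6. State that adjustment cannot remove a secular trend in this design.

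Fix the model before second-phase outcomes are seen. The cost is revised wording, a little more analysis and some dependence on the model. No additional patients are proposed; the documents do not give the between-site variation or covariate effects needed to recompute the sample size for the adjusted analysis.

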### Total Number of Study Sites/Total Number of Subjects Projected:

Seven sites/~1000-1500 patient data per site projected.

Central coordinating site: All India Institute of Medical Sciences (AIIMS Bathinda)

- PI: [name], Assistant Professor, Pharmacology, AIIMS Bathinda
- Co-PI: [name], Associate Professor, Anaesthesia, AIIMS Bathinda; [name] [name], Additional Professor, General Surgery, AIIMS Bathinda

Other participating sites:

- Postgraduate Institute of Medical Education and Research, Chandigarh (PGIMER Chandigarh)

Site PI: [name] [name], Associate Professor, Pharmacology, PGIMER Chandigarh

Site Co-PI: [name] [name], Assistant Professor, General Surgery, PGIMER Chandigarh

- Postgraduate Institute of Medical Sciences (PGIMS Rohtak)

Site PI: [name], Associate Professor, Pharmacology, PGIMS Rohtak

Site Co-PI: [name], Professor, General Surgery, PGIMS Rohtak

- Dayanand Medical College, Ludhiana

Site PI: [name], Professor, Pharmacology, DMC Ludhiana

Site Co-PI: [name], Professor and Head of Department, General Surgery, DMC Ludhiana

- Government Medical College & Hospital, Sector-32, Chandigarh (GMCH-32)

Site PI: [name], Professor, General Surgery, GMCH-32, Chandigarh

Site Co-PI: [name], Associate Professor, General Surgery, GMCH-32, Chandigarh

- Jawaharlal Nehru Medical College (JNMC), AMU, Uttar Pradesh

Site PI: [name] [name], Assistant Professor, Pharmacology, JNMC, AMU

Site Co-PI: [name] [name], Assistant Professor, Department of Surgery, JNMC, AMU

[name] [name], Department of Orthopedics, JNMC, AMU

- [name] Medical College, Hamirpur, Himachal Pradesh (H.P)

Site PI: [name], Associate Professor, General Surgery, [name] Medical College, Hamirpur

Site Co-PI: [name], Assistant Professor, Orthopedics, [name] Medical College, Hamirpur

- [name], Professor, Indian Institute of Management, Calcutta
- [name], Professor, Department of Community Medicine, Government Medical College, Manjeri, Malappuram, Kerala.

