## Sample Size and Power

The three strata based on the type of the surgery (clean, clean-contaminated and contaminated) will be separately powered, based on different baseline SSI rates extracted from Indian study showing prevalence of SSIs in general surgery patients.^7,8^ The sample sizes were based on 90% power, a 5% two-sided significance level and 15% loss to follow up or death before reaching the primary endpoint at 30-days. For the clean surgeries, anticipating the baseline average SSI rate of 8%, a 3% absolute reduction in SSI to 5% will be taken as clinically significant and would require 3260 patients in total (1630 patients in pre-intervention and intervention each). For the clean-contaminated surgeries, anticipating the baseline average SSI rate of 12%, a 4% absolute reduction in SSI to 8% will be taken as clinically significant (i.e relative risk of 0.67) and would require 2700 patients in total (1350 in pre-intervention and intervention each). For the contaminated surgeries, anticipating higher baseline SSI rate of 30%, a 10% absolute reduction in SSI to 20% will be taken as clinically significant and would require 900 patients in total (450 in pre-intervention and intervention each).

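### The pre-post tests and the sample sizes ignore site, so with seven sites the 5% error rate and the 90% power are not assured

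*Protocol*

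**What the plan says.** Section 3.9 compares post-intervention with baseline outcomes at the study centres, separately in clean, clean-contaminated and contaminated surgery. For these comparisons, "Chi-square test, independent sample t test or Mann-Whitney U test will be used for the statistical comparisons". Of the three, only the chi-square test fits a yes/no infection outcome. The section also names log-rank tests (for wound class or other exposure categories) and a Cox model for predictors. Neither is said to account for site.

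Section 3.11 powers each wound class separately: "The sample sizes were based on 90% power, a 5% two-sided significance level and 15% loss to follow up or death". The clean stratum "would require 3260 patients in total (1630 patients in pre-intervention and intervention each"), the clean-contaminated stratum "would require 2700 patients in total (1350 in pre-intervention and intervention each"), and the contaminated stratum needs 900 (450 per phase). It mentions no intraclass correlation, design effect or site.

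Section 3.3.2 projects "Seven sites/~1000-1500 patient data per site projected". Section 3.1.3 provides for champions in each setting, re-training where a site does not comply, and adaptation of the package to a site's needs if non-compliance persists. Section 3.5.1 ends data collection at sites that do not comply.

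**The concern.** The intervention acts on hospitals and their staff. Infection rates at one hospital tend to move together between two periods, through staffing, theatre conditions, case mix, quality of follow-up or local uptake of the package. With only seven sites, such site-specific movements need not average out. A test that counts every patient as independent information does not see them, so its standard error is too small. Pooling without a site term has a second weakness: if a site's share of patients changes between phases, most plainly when a site is terminated after baseline, a shift in mix can look like an effect.

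This is the confirmatory comparison in all three separately powered strata, so the stated error rate and power both depend on it.

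**Working it through.** **Inputs from the protocol.** Rates of 8% to 5% (clean), 12% to 8% (clean-contaminated) and 30% to 20% (contaminated); two-sided 5%; 90% power; 15% loss; seven sites; 1630, 1350 and 450 patients per phase.

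**Step 1: reproduce the stated sizes.** For two independent proportions, with p̄ the mean of p1 and p2:

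n = [1.96·√(2p̄(1−p̄)) + 1.2816·√(p1(1−p1)+p2(1−p2))]² / (p1−p2)²

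Clean: (1.96·0.3486 + 1.2816·0.3480)² / 0.0009 ≈ 1417. The same formula gives about 1180 for clean-contaminated and 392 for contaminated. Multiplied by 1.15, these are about 1630, 1357 and 451, against the stated 1630, 1350 and 450. The sizes therefore follow from independent patients, a design effect of 1. After 15% loss from the stated numbers, power under independence is about 89% in each class.

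**Step 2: patients per site and phase.** m = 0.85·N/7, assuming equal sites: 0.85·1630/7 = 197.9 (clean), 0.85·1350/7 = 163.9 (clean-contaminated), 0.85·450/7 = 54.6 (contaminated).

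**Step 3: what cancels and what does not.** With the same sites in both phases, the design effect is

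DE = 1 − ICC + m·ICC·(1 − CAC)

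where CAC is the correlation of a site's effect between phases. If CAC = 1 and the site mix is unchanged, DE is 0.98 to 0.995 for ICC 0.005 to 0.02. Type I error is then 4.8 to 4.9% and power about 89 to 90%, so nothing is lost. The nominal error is exceeded once CAC falls below about 0.995 (clean), 0.994 (clean-contaminated) or 0.982 (contaminated). As an assumed example, ICC 0.01 and CAC 0.8 in clean surgery give DE = 0.99 + 197.9·0.01·0.2 = 1.39 and a type I error of 2·[1 − Φ(1.96/√1.39)] = 9.6%.

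**Step 4: simulation over an assumed range.** Seven equal sites, between-site SD 0.3, and independent site-by-phase deviations with the SD shown, all on the log-odds scale. Both SDs are assumptions. Type I error of the pooled chi-square:

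| Site-by-phase SD | Clean | Clean-contaminated | Contaminated |
|---|---|---|---|
| 0 | about 5% | about 5% | about 5% |
| 0.1 | 7% | 7% | 6% |
| 0.2 | 12% | 14% | 10% |
| 0.3 | 21% | 23% | 17% |

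Analytic cross-check, clean, SD 0.2: net correlation ≈ 0.2²·0.08·0.92 = 0.0029; DE ≈ 1 + 196.9·0.0029 ≈ 1.58; type I error ≈ 2·[1 − Φ(1.96/1.26)] ≈ 12%.

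**Step 5: power in clean surgery.**

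| Site-by-phase SD | Planned chi-square | Paired t-test on 7 site log-odds differences (6 df) |
|---|---|---|
| 0 | 89 to 90% | 74% |
| 0.1 | 89% | 69% |
| 0.2 | 86% (84 to 86% in repeat runs) | 58% |
| 0.3 | 81% | 45% |

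The paired test holds 5% throughout. The chi-square keeps more power because it no longer holds 5%.

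**Step 6: site mix.** If one of the seven sites is lost after baseline (ICC 0.01, CAC 1), type I error is 6.8% (clean), 6.3% (clean-contaminated) and 5.4% (contaminated).

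**The case against.** The strongest reply is that the design already protects itself: each site is its own comparator, so stable differences between hospitals drop out. That is right. A reader might infer that the 5% and 90% definitely fail, or that the usual inflation 1 + (m−1)·ICC applies in full. The protocol supports neither. With stable sites and balanced mix, both figures hold.

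A reader might also infer that the planned test's power falls to between 78% and 46% in clean surgery. Those values come from dividing n by design effects of 1.39 and 2.97, so they describe a variance-corrected test, not the chi-square. The lower one also needs a net correlation of 0.01, an SD of about √(0.01/0.0736) = 0.37, which is beyond the range above. Likewise, the 74% at SD 0 is no defect of the plan; it is partly the price of a 6-df test.

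Three further points have weight:
- If the intervention has no effect at any site, differing effects cannot raise the type I error; only site-specific change over time or a change in mix can. If inference is confined to these seven centres, differing effects are not sampling error. The package is also meant to be standardised, with adaptation only after persistent non-compliance.
- An SD of 0.3 is severe. It implies an SD of √2·0.3 = 0.42 in each site's log-odds change, against a planned clean effect of about 0.50.
- Section 3.9 does not assign the chi-square to the primary endpoint by name and expresses infection per person-time. A separate analysis plan could add a site term.

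These points limit the size and certainty of the problem. They do not remove it: every comparison test the protocol names assumes independent patients, and a separate analysis plan would not by itself correct the power statement in Section 3.11.

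**Conclusion.** The concern holds in conditional form: the 5% error rate and 90% power are not assured. The main exposure is excess false positives, not lost power of the planned test. At an assumed site-by-phase SD of 0.2, type I error is more than double the nominal level in clean and clean-contaminated surgery and about double in contaminated surgery; at 0.1 the excess is one to two percentage points. A test that does hold 5% has clearly less than 90% power in clean surgery.

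All these sizes rest on assumed variation, equal sites and 15% loss; the protocol gives no ICC or between-phase correlation. What it does establish is that site enters neither the test nor the sample size, while its own delivery, re-training, adaptation and termination rules make site-by-phase variation and mix changes likely. This should be fixed, but it does not invalidate the design.

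**What to change.** In Section 3.9, make the primary comparison in each wound class a regression (logistic or modified Poisson) with phase as the exposure, site as a fixed effect and a random site-by-phase effect. Use small-sample inference suited to seven sites: 14 site-phase cells less seven site terms and one phase term leave 6 df. The fixed site term deals with changes in mix; it does not by itself deal with site-by-phase variation. Add a site-level paired analysis as a check.

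In Section 3.11, replace the flat 90% with power over a stated, assumed range of site-by-phase variation. Phase-I data can inform the site rates for this, but one baseline phase cannot show how sites vary between phases, so that part remains an assumption.

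The cost is a change of wording, wider confidence intervals and a less favourable power figure. No extra patients are needed for the change itself, but it does not restore 90% power. It should be settled before post-intervention data are compared with baseline.

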# Study Objectives

## Primary Objective (or AIM):

To evaluate the effect of multipronged interventions on rate of surgical site infections in clean, clean-contaminated, contaminated surgeries (Refer to Appendix III for definitions). (Multipronged intervention components mentioned in section 3.6)

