## Secondary Objectives (or AIM)

1. To identify the system and health care professional behavioral factors contributing to surgical site infections
2. To co-develop multipronged interventions which can be applied in hospital settings in LMICs
3. To evaluate the impact of multipronged interventions on in-patient mortality and length of hospital stay
4. To evaluate the number of deaths prevented by adoption of multipronged interventions
5. To evaluate the number of ICU admissions averted and number of hospital readmissions averted within 30 days after discharge by adoption of multipronged interventions
6. To evaluate the effect of multipronged interventions on the antimicrobial consumption indicators Days of therapy (DOT).

[Days of therapy is defined as an aggregate sum of days for which any amount of a specific antimicrobial agent was administered to individual patient^13^]

1. To evaluate the percentage of patients receiving the correct surgical antimicrobial prophylaxis.
2. To evaluate the acceptance of these multipronged interventions and challenges in their implementation by health care professionals using in-depth interviews and a qualitative feedback assessment form.

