## Secondary Endpoints

1. The number of ICU admissions averted and number of readmissions averted in clean, clean-contaminated and contaminated surgeries by adoption of multipronged interventions
2. The length of index hospital admission in pre-intervention and intervention phase for clean, clean-contaminated and contaminated surgeries.
3. The antimicrobial consumption indicators (Days of therapy) in the pre-intervention and intervention phase for clean, clean-contaminated and contaminated surgeries.
4. The percentage of patients receiving single dose of antimicrobial prophylaxis in the pre-intervention and intervention phase for clean, clean-contaminated and contaminated surgeries
5. The percentage of patients receiving prolonged antimicrobial prophylaxis (>24 hours duration) in the pre-intervention and intervention phase for clean, clean-contaminated and contaminated surgeries
6. The percentage of irrational combinations of drugs (double gram positive, double gram negative or double anaerobic coverage) for surgical antimicrobial prophylaxis in the pre-intervention and intervention phase for clean, clean-contaminated and contaminated surgeries
7. The number of deaths prevented in clean, clean-contaminated and contaminated surgeries by adoption of multipronged interventions
8. Acceptance of these multipronged interventions and challenges in their implementation by healthcare professionals.

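### Deaths, ICU admissions and readmissions have overall objectives but only by-wound-class comparisons: add one estimate stratified by wound class for each outcome

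*Protocol*

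**What the plan says.** Section 2.2 states two of the objectives as "To evaluate the number of deaths prevented by adoption of multipronged interventions" and "To evaluate the number of ICU admissions averted and number of hospital readmissions averted within 30 days after discharge by adoption of multipronged interventions". Objective 3 adds in-patient mortality, also with no wound class. The primary objective, by contrast, does name the classes: "To evaluate the effect of multipronged interventions on rate of surgical site infections in clean, clean-contaminated, contaminated surgeries".

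The endpoints in section 3.8 move to the class level: "The number of ICU admissions averted and number of readmissions averted in clean, clean-contaminated and contaminated surgeries by adoption of multipronged interventions" (endpoint 1) and "The number of deaths prevented in clean, clean-contaminated and contaminated surgeries by adoption of multipronged interventions" (endpoint 7).

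Section 3.9 then says "The analysis will be conducted separately for clean, clean-contaminated and for contaminated surgeries". The tests offered are general: "Chi-square test, independent sample t test or Mann-Whitney U test will be used for the statistical comparisons". For a binary outcome that means a chi-square test of pre against post.

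Section 3.11 sizes each class on its own, for SSI: "The sample sizes were based on 90% power, a 5% two-sided significance level and 15% loss to follow up". It gives no rate, target effect or power for death, ICU admission or readmission.

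**The concern.** The objectives pose one question per outcome: does the package reduce deaths, ICU admissions and readmissions, and by how many? The planned comparison gives three separate answers per outcome and no overall one with an interval. The reason for splitting is that baseline SSI risk differs by class and each class was sized for SSI. That reason does not carry over to outcomes for which no sizing was done.

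If the proportional effect is similar across classes, each class result may be inconclusive while the classes taken together are informative. And if no combined estimate is fixed in advance, choosing between by-class and pooled results after seeing the data is left open.

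This is a question of precision and of matching analysis to objective for secondary outcomes. It is separate from the error rate of the three primary SSI tests.

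**Working it through.** **1. The protocol's own sample sizes.** Per phase, with p̄ the mean of the two rates:

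n = [1.96·√(2p̄(1−p̄)) + 1.2816·√(p1(1−p1) + p2(1−p2))]² / (p1−p2)²

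| Class | SSI rates | n | n × 1.15 | Stated in 3.11 |
|---|---|---|---|---|
| Clean | 8% vs 5% | 1418 | 1631 | 1630 |
| Clean-contaminated | 12% vs 8% | 1181 | 1359 | 1350 |
| Contaminated | 30% vs 20% | 392 | 451 | 450 |

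The stated sizes reproduce closely, and they are SSI calculations only. They total 1630 + 1350 + 450 = 3430 per phase, so the classes hold 48%, 39% and 13% of the patients.

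**2. Inputs for the other outcomes.** Evaluable patients per phase are 0.85 × 1630, 1350 and 450, about 1385, 1147 and 382. Event rates and the relative risk (RR) are assumptions, because the protocol gives none.

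**3. Formulas.** Within class i, d = p1 − p2 with p2 = RR × p1. The null standard error is √(2p̄(1−p̄)/n) and the alternative one is √((p1(1−p1) + p2(1−p2))/n). Power = Φ((d − 1.96·SE0)/SE1). For the combined test, d and the variances are taken across classes with Mantel-Haenszel weights n1n2/(n1+n2). With equal phases these are proportional to class size.

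**4. Worked case: readmission 5/8/12%, RR 0.75.** The differences are 1.25, 2.00 and 3.00 points, with standard errors of 0.78, 1.06 and 2.21 points. The combined difference is 0.475 × 1.25 + 0.394 × 2.00 + 0.131 × 3.00 = 1.77 points. Its standard error is √((0.475 × 0.78)² + (0.394 × 1.06)² + (0.131 × 2.21)²) = 0.63 points. The 95% half-widths are 1.5, 2.1 and 4.3 points by class and 1.2 combined.

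**5. Power under assumed rates** (clean / clean-contaminated / contaminated):

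| Assumed outcome and rates | RR | By class | Combined |
|---|---|---|---|
| Readmission 5/8/12% | 0.75 | 36 / 47 / 27% | 81% |
| Readmission 3/5/10% | 0.75 | 23 / 31 / 23% | 62% |
| ICU admission 2/4/10% | 0.75 | 17 / 26 / 23% | 54% |
| Death 0.5/1.5/4% | 0.75 | 7 / 12 / 11% | 22% |
| Readmission 3/5/10% | 0.67 | 38 / 51 / 38% | 87% |
| ICU admission 2/4/10% | 0.67 | 27 / 42 / 38% | 79% |
| Any outcome, 10% in every class | 0.67 | 88 / 82 / 38% | >99% |

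The value 0.67 is the ratio that section 3.11 uses for SSI in clean-contaminated surgery. All these figures ignore clustering by site, which affects both approaches.

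**6. Effect through SSI only.** Section 1.1 says that infected patients have twice the mortality and are 60% more likely to be admitted to ICU. If the package acts only by lowering SSI from a to b, the implied ratio is RR = (1 + x·b)/(1 + x·a), with x = 1 for death and x = 0.6 for ICU admission.

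- Death: 1.05/1.08 = 0.97, 1.08/1.12 = 0.96, 1.20/1.30 = 0.92.
- ICU admission: 1.030/1.048 = 0.98, 1.048/1.072 = 0.98, 1.12/1.18 = 0.95.

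Take a risk of 1 to 10% in uninfected patients and all 3430 per phase. Power for death is then 5 to 7% by class and 5 to 9% combined. For ICU admission it is 5 to 6% either way.

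**7. Absolute precision is not always better.** For death at 0.5/1.5/4% and RR 0.75, the combined half-width is 0.55 points, against 0.49 in the clean class alone. The combined test is still stronger, because the combined difference is 0.34 points against 0.125 in the clean class (0.5% × 0.25).

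**The case against.** The strongest reply is that there is no contradiction. Endpoints 1 and 7 put the objectives into operation by class, and the analysis and sizing follow them. Objectives are usually shorter than endpoints, and a combined summary could be added in a separate statistical analysis plan. Section 3.9 does not forbid one. This stands in part: it makes the point an improvement, not an error. But section 3.9 makes a positive choice of separate analysis, and its stated rationale covers SSI only.

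It is also true that numbers averted can be added. With equal phases, the Mantel-Haenszel risk difference equals the summed numbers averted divided by total patients. In the worked case, 1385 × 1.25% + 1147 × 2% + 382 × 3% ≈ 52, and 52/2914 ≈ 1.8%. The overall point estimate is therefore recoverable. What is not planned is its interval or test.

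A reader might infer more than the protocol supports:

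- *These outcomes are rare and most of the power is thrown away.* The protocol gives no rates. ICU admission need not be rare when neurosurgery and emergency cases are included. At 10% and RR 0.67, two classes already have more than 80% power.
- *Every analysis is split by class.* Section 3.9 also plans a log-rank comparison between the classes, which must span them, although for SSI.
- *Combining would rescue these endpoints.* Under the SSI-only calculation it would not do so for death or ICU admission. Even at RR 0.75, combined power is 54%, 62% and 22% in three of the four scenarios.

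Against the SSI-only calculation, the template package in Appendix-I also covers antimicrobial use, glucose control and normothermia, so the effect need not run through SSI alone.

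**Conclusion.** The point holds as a low-cost improvement. Objectives 3 to 5 are overall questions, and the plan names no combined pre/post estimate, interval or test for death, ICU admission or readmission. The gain from adding one depends on assumptions that the protocol cannot settle. With a common RR of 0.75 and the assumed rates above, power rises from about 7 to 47% by class to 22 to 81% combined. With an effect through SSI alone, it stays below 10% for death and ICU admission under either approach. The case for the combined estimate therefore rests first on answering the stated objective with an interval, and only second on power. A common relative effect across classes is assumed throughout.

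**What to change.** In section 3.9, keep the three by-class results and add one pre/post estimate for each of death, ICU admission and readmission, stratified by wound class. A Mantel-Haenszel risk ratio with the corresponding standardised risk difference would serve, as would a regression with wound class as a term. Report the 95% confidence interval, and derive the overall numbers of deaths prevented and admissions averted from this estimate. Stratify instead of pooling crudely, so that a change in class mix between phases does not distort the comparison. Align objectives 3 to 5 with endpoints 1 and 7 by saying that both overall and by-class results are intended.

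The cost is a sentence or two of wording and a few lines of code, with no new data. There are two downsides to state. The combined figure averages over classes using the recruited mix (about 48/39/13%), which comes from the SSI sample sizes and not from a stated hospital case mix; the by-class results beside it will show any differing effects. And the absolute risk difference is not always more precise than that of the lowest-risk class.
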